## Abstract

Introduction: Heart transplant (HT) survival has barely improved in the last decades, which is unsatisfactory for many HT recipients. The development of anti-human leukocyte antigen (anti-HLA) antibodies in HT patients is associated with a cardiac allograft dysfunction. The mechanisms leading to this damage are unclear. The Multimodality Evaluation Of Antibody-Mediated Injury In Heart Transplantation (LEONE-HT) study aimed to thoroughly describe the damage inflicted on the myocardium by anti-HLA antibodies. Methods and analysis: The LEONE-HT study is a cohort study with a cross-sectional approach in which HT patients with positive anti-HLA antibodies are compared with coetaneous HT patients with negative anti-HLA antibodies. All patients will undergo a state-of-the-art multimodal assessment, including imaging techniques, coronary anatomy and physiology evaluations and histological and immunological analyses. The individual and combined primary outcomes of structural graft injuries and longitudinal secondary outcomes are to be compared between the exposed and non-exposed groups with univariate and multivariable descriptive analyses. Ethics and dissemination: The LEONE-HT study is carried out in accordance with the principles set out in the Declaration of Helsinki and the International Conference on Harmonization guidelines for good clinical practice and following national laws and regulations. The study design, objectives and participant centers have been communicated to clinicaltrials.gov (NCT05184426). The LEONE-HT study counts on the support of patient associations to disseminate the objectives and results of the research. This study was funded by the Spanish Ministry of Science and Innovation and the Spanish Society of Cardiology.

## 1. Strengths and Limitations of This Study

-The appearance of anti-HLA antibodies is known to be related to poorer outcomes, suggesting that anti-HLA antibodies induce chronic graft damage beyond acute rejection.-The LEONE-HT project aimed to describe the structural damage inflicted on the myocardium by anti-HLA antibodies and test the performance of different diagnostic techniques to identify and grade antibody-mediated injuries in HTs.-Patients underwent a complex multimodal assessment, including state-of-the-art histopathologic, physiologic and imaging techniques.-Our study limitations were inherent to the observational approach as the selection of non-exposed patients was the most complex part of the study.-This pilot study aimed to define antibody-mediated damage in HT thoroughly and set the basis for future dedicated studies in the field.

## 2. Introduction

Heart transplantation (HT) is the last therapeutic alternative for many patients with heart failure [1]. In recent years, the short-term survival for HT patients has markedly improved (85–90% survival rate in the first year after HT). However, the long-term survival has barely improved, remaining around 11 years [2]. Although there are many risk factors related to a late allograft dysfunction, the detection of anti-human leukocyte antigen (anti-HLA) antibodies is true for half of the patients [3,4] and the detection of donor-specific antibodies constitutes an independent predictor of a poorer survival in this population [5].

The management of patients with anti-HLA antibodies is not well-defined due to the lack of solid evidence, with no reliable data about “which antibodies are of clinical relevance, which patients to treat, and which treatments are most effective or safe” [6]. Thus, although the treatment of acute antibody-mediated rejection is well-established, there is a lack of evidence for managing chronic antibody-mediated injuries [7]. The current follow-up work-up of HT patients includes echocardiography, coronary angiography and an endomyocardial biopsy. The appearance of de novo anti-HLA antibodies with an otherwise normal work-up is relatively common. However, most of these patients finally develop a graft dysfunction. In this scenario, and for many patients, there are no appropriate treatments and re-transplantation is the only option. Nowadays, there is a trend towards a more aggressive approach to these patients to better understand the pathophysiology of the process. This often leads to the performance of the coronary angiography, right-heart catheterization and endomyocardial biopsy out of the established protocols.

This is why a detailed description of antibody-mediated chronic injuries is a necessary first step to lead us to develop evidence-based diagnostic and care protocols. 

An antibody-mediated injury is produced through the activation of the complement system, which leads to leukocyte migration, increased phagocytosis and a T cell-mediated immune response. The rapamycin pathway promotes cytoskeletal remodeling and immune cell proliferation and migration. This immune response finally leads to allograft vasculopathy and a late allograft failure. The time from the antibody detection to myocardial damage varies between patients from a few months to several years [8].

The vascular wall is an interface between the graft and the immune system of the recipient. The evidence suggests that antibody-mediated injuries are predominantly related to vascular damage [9]. In kidney transplantations, the use of transmission electron microscopy (TEM) offers a detailed description of the antibody-mediated injury where endothelial damage can be identified with endothelial cell enlargement and vacuolization, subendothelial widening and the duplication of the basal membrane. Therefore, the use of TEM has been included in the evaluation of antibody-mediated rejection in kidney transplant patients [10].

Conversely, the diagnosis of antibody-mediated injuries in HT relies solely on optic microscopy (OM) and immunohistochemistry (IHC) techniques [11] because a TEM-based description is unavailable. 

In this study, we aimed to describe the tissue damage inflicted on the myocardium by anti-HLA antibodies in heart transplant patients through a multimodal evaluation, including advanced imaging techniques, tissue and immunological analyses and coronary anatomical and physiological assessments. 

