### 3.2. Study Population

Our study base is a large dynamic cohort of HT patients assembled in the region of Madrid, Spain. All patients have received an HT and continue their follow-up in one of the three participating centers: University Hospital 12 de Octubre; University Hospital Gregorio Marañón; and University Hospital Puerta de Hierro. The local protocols for the follow-up and treatment of the HT patients are equivalent for the three participating centers. 

For every HT patient in whom anti-HLA antibodies are detected at or since the start of the study (exposed), we will select a comparator (non-exposed) with negative anti-HLA antibodies, a normal functioning graft and whose HT date is close to that of the exposed patient (Figure 2).

A confirmatory test for every patient with positive anti-HLA antibodies will be performed at least three months after the first determination and before the multimodal assessment. A regular anti-HLA antibody determination is performed as part of the local follow-up protocols for HT patients to confirm the patient allocation before evaluating the outcomes for the secondary endpoint. 

All patients will be appropriately informed about the risks of the scheduled test. For the selection of non-exposed patients, we will prioritize those patients who had a routine assessment planned within the local follow-up protocol (especially for the invasive tests).

With the inclusion of a contemporary case of an HT comparator patient (with negative anti-HLA antibodies), we will reduce the possibility of a bias induced by shorter or longer follow-up periods that may under- or over-estimate the effect of anti-HLA antibodies in myocardial injuries. The inclusion and exclusion criteria are defined in Table 1. 

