### 3.4. Study Design

We designed a cross-sectional approach to address the primary objective of this project. 

All exposed and non-exposed participants will undergo a multimodal evaluation that consist of an endomyocardial biopsy and analyses with OM, TEM and IHC as well as transthoracic echocardiography and CMR, right-heart catheterization, coronarography, IVUS, a pressure guidewire assessment, an immunological study and the determination of the serum markers of fibrosis (Figure 2). 

The three participating hospitals are responsible for the patient recruitment and follow-up. The hemodynamic study tissue and blood sampling will be also performed at the recruiting center, according to an *ad hoc* protocol. The Spanish National Center for Cardiovascular Research acts as the imaging core lab, where every included patient is transferred for the imaging acquisition and further analysis. A multidisciplinary team consisting of pathologists, interventional cardiologists, cardiac imaging experts, immunologists and biologists of the host institution (University Hospital 12 de Octubre) will analyzed all performed tests (Figure 2). Those specialist responsible for the analysis are blind to the anti-HLA antibody exposure status of the participants. 

Figure 3 summarizes the timeline and the achieved milestones of this research project. 

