### 3.5. Assessment Variables

Primary outcomes: individual and combined structural graft injury outcomes based on the presence of microvascular inflammation, intimal or transmural arteritis or thrombotic microangiopathy (OM); linear C4d staining (%) (IHC); and endothelial edema and vacuolization (semi-quantitative score), subendothelial widening (pm) and basal membrane duplication (TEM). For the secondary objectives: ○Microvascular damage assessment: Index of microcirculatory resistance and coronary flow reserve (pressure guidewire), a CMR-based quantitative perfusion assessment (mL/min/100 g of tissue) and the capillary density (capillaries/mm^2^) (OM).○CMR T2 mapping (ms) to detect intracellular edemas (endothelial vacuolization).○CMR T1 mapping (ms) and CMR extracellular volume quantification (%) as well as TTE-based global longitudinal strain (%) to identify myocardial remodeling and fibrosis.○Fibroblast growth factor 23 (R.U./mL), procollagen type 1 carboxy-terminal propeptide (µg/L) and collagen type 1 C-terminal telopeptide (µg/L) as the serum markers of fibrosis and remodeling.○FFR (coronary physiology) and IVUS-based intimal thickness (mm) as early markers of coronary allograft vasculopathy. ○Rate of antibody-mediated rejection, anti-HLA antibody seroconversion, heart failure and death. 

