### 3.6. Data Collection and Statistical Analysis 

The study data are collected and managed using REDCap electronic data capture tools hosted at the Instituto de Investigación Sanitaria Hospital 12 de Octubre (imas12). REDCap (Research Electronic Data Capture) is a secure, web-based software platform designed to support data capture for research studies [20,21]. 

A clinical research coordinator (CRC) conducts the data management at the host institution. The CRC is responsible for reviewing the eCRFs and ensuring compliance with the registration protocol. Of the sample, 10% will be randomly selected for the data verification. 

The individual and combined primary outcomes of the structural graft injury and longitudinal secondary outcomes will be compared between the exposed and non-exposed groups with univariate and multivariable descriptive analyses. The predictive performance of CMR, TTE, coronary physiology parameters and IVUS will be assessed with univariate and multivariable modelling. A parsimonious approach will be implemented to propose a standard assessment protocol, including a predictive score based on the study results. All statistical analyses will be obtained using dedicated software (StataCorp. 2021. Stata Statistical Software: Release 17. StataCorp LLC., College Station, TX, USA).

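### The between-group comparison of antibody-mediated rejection is open to surveillance bias, because antibody-positive patients are, by the protocol's own account, often biopsied off schedule

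*Protocol article*

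**What the plan says.** Section 3.5 (Assessment Variables) ends its list for the secondary objectives with: "Rate of antibody-mediated rejection, anti-HLA antibody seroconversion, heart failure and death". Section 3.6 states that "longitudinal secondary outcomes will be compared between the exposed and non-exposed groups with univariate and multivariable descriptive analyses". The article does not itemise which outcomes are longitudinal, but the event rates in that last bullet are the natural reading.

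Two statements in the Introduction bear on how AMR is found. On diagnosis: "the diagnosis of antibody-mediated injuries in HT relies solely on optic microscopy (OM) and immunohistochemistry (IHC) techniques". On practice, after describing patients who develop de novo antibodies with an otherwise normal work-up: "Nowadays, there is a trend towards a more aggressive approach to these patients", followed by "This often leads to the performance of the coronary angiography, right-heart catheterization and endomyocardial biopsy out of the established protocols".

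Three statements could act as safeguards:

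- Section 3.4 gives every participant, exposed or not, the same multimodal evaluation, including an endomyocardial biopsy.
- Section 3.4 adds: "Those specialist responsible for the analysis are blind to the anti-HLA antibody exposure status of the participants".
- Section 3.2 says: "The local protocols for the follow-up and treatment of the HT patients are equivalent for the three participating centers".

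**The concern.** The exposure may influence how often the outcome is looked for. If a positive antibody test alone leads to extra biopsies, exposed patients have more opportunities for AMR to be detected, including episodes that would go unseen in a comparator with the same disease. Some of any excess of AMR in the exposed group would then reflect sampling effort. The bias favours the study's hypothesis, so a positive result would raise no suspicion.

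The AMR rate is also one of the few outcomes here with direct clinical meaning, and the article says it intends to inform diagnostic protocols. A ratio that mixes biology with surveillance would be a poor basis for that.

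**Working it through.** **Step 1: is there a figure to reproduce?** No. The article gives no expected AMR rate, no follow-up biopsy frequency and no count of off-schedule biopsies. The sample-size figures in Section 3.3 concern endothelial damage on electron microscopy and intimal thickness on intravascular ultrasound, not AMR.

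**Step 2: do the stated safeguards reach the problem?**

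| Safeguard | What it equalises | What it leaves open |
|---|---|---|
| Common study biopsy (3.4) | One biopsy per patient, hence the cross-sectional primary outcome | Number of biopsies during follow-up |
| Blinded analysis (3.4) | Reading of the study tests | The decision to biopsy. The recruiting hospitals carry out follow-up (3.4), and regular antibody testing is part of their local protocols (3.2) |
| Equivalent local protocols (3.2) | Practice between centres | Practice between exposure groups; the Introduction speaks of biopsies outside protocols |

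None of the three equalises biopsy frequency between exposed and non-exposed patients in follow-up.

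**Step 3: how large could the effect be?** All inputs here are assumptions. Both models give the two groups the same true risk, so the correct ratio is 1.0.

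*Model A: each biopsy is an independent chance q of finding AMR.* Detected proportion = 1 − (1 − q)^k for k biopsies.

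| q | k = 1 | k = 2 | k = 3 | Ratio 2 vs 1 | Ratio 3 vs 1 |
|---|---|---|---|---|---|
| 3% | 3.0% | 5.9% | 8.7% | 1.97 | 2.91 |
| 5% | 5.0% | 9.8% | 14.3% | 1.95 | 2.85 |
| 10% | 10.0% | 19.0% | 27.1% | 1.90 | 2.71 |

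*Model B: an episode is present with probability P, and each biopsy finds it with sensitivity s.* Detected proportion = P × [1 − (1 − s)^k]. P cancels in the ratio.

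- s = 0.5: 0.75/0.50 = 1.50 for 2 vs 1, and 0.875/0.50 = 1.75 for 3 vs 1.
- s = 0.7: 0.91/0.70 = 1.30 for 2 vs 1, and 0.973/0.70 = 1.39 for 3 vs 1.

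With equal biopsy numbers both models return 1.0. If both groups have more biopsies, the distortion shrinks: in model A at q = 5%, 2 vs 3 biopsies gives 14.3%/9.8% = 1.46.

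**Step 4: scale in patients.** With the planned 45 per group and model A at q = 5%, one vs three biopsies gives 45 × 0.050 = 2.3 against 45 × 0.143 = 6.4 expected patients with detected AMR. A few extra biopsies could move the comparison noticeably.

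**The case against.** The best case for the plan has several parts.

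- **The Introduction describes a trend in practice, not a study procedure.** This stands. Section 3 prescribes no additional biopsies for exposed patients, and no imbalance at the three hospitals is reported. The point is therefore about an open risk, not a demonstrated imbalance.
- **A reader might infer that any excess of AMR in exposed patients is purely an artefact of looking harder.** The document does not support that. A true antibody effect is the study's hypothesis and may coexist with surveillance bias.
- **A reader might infer from Section 3.2 that comparators will be biopsied less in follow-up, since those already due for a routine work-up are preferred.** That sentence concerns who is selected for the study assessment. It says nothing about later biopsy frequency.
- **A reader might infer that AMR found on the study biopsy will be counted again as a secondary event.** No text says so. Section 3.6 calls the secondary outcomes longitudinal, and Section 3.2 places their evaluation after a further check of allocation. The article only leaves open whether the two are kept apart.
- **A reader might carry the ratios over to the objective on risk by time from antibody positivity (3.1).** They do not apply: non-exposed patients have no date of positivity, so a between-group ratio does not measure bias there.
- **The full protocol or analysis plan, not shown, may deal with this, and the analyses are descriptive within a self-described pilot.** Both are fair and limit the weight of the point. Still, the article itself commits to the comparison and itself describes exposure-dependent biopsy. The limitations in Section 1 name the observational approach and the choice of non-exposed patients, not unequal ascertainment.

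**Conclusion.** The point holds as a risk of bias in one secondary comparison. Three statements in the article combine to produce it: AMR is compared between groups, diagnosis needs tissue, and antibody-positive patients are often biopsied off schedule. The stated safeguards protect the blinded, cross-sectional primary outcome but do not equalise sampling in follow-up.

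The direction is clear, namely inflation of AMR in the exposed group. The size is not known. The range of roughly 1.3 to 2.9 rests on assumed biopsy counts (one against two or three), an assumed yield of 3–10% or sensitivity of 0.5–0.7, and equal true risk. The upper end needs independent chances at each biopsy, while the missed-episode model stays at 1.3 to 1.75. It should be corrected because it is cheap to correct, and because the reason for a biopsy may be hard to recover later if it is not recorded at the time.

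**What to change.** In Sections 3.5 and 3.6, without changing who is biopsied or when:

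1. Record the reason for every biopsy in the eCRF: routine schedule, symptoms or graft dysfunction, or antibody status only.
2. Report biopsies per patient-year by group.
3. Present the AMR comparison twice, side by side: on all biopsies, and on routine-schedule plus symptom- or dysfunction-prompted biopsies. Show AMR found on biopsies prompted only by antibody status separately.
4. Report AMR on the common, blinded study biopsy as its own cross-sectional result, not pooled with AMR events in follow-up. It should not be discarded: it is the one biopsy that both groups receive under the same procedure and with blinded reading, so it is the AMR ascertainment least exposed to this bias.

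The cost is one eCRF item and some analysis wording. The restricted comparison will have fewer events. It may also under-count true AMR in exposed patients, because an episode found on an antibody-prompted biopsy may never appear on a scheduled one. The two results can therefore err in opposite directions, which is the reason to show both.

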## 3. Methods and Analysis

### 3.1. Study Hypotheses and Objectives

Graft injuries related to a chronic exposure to anti-HLA antibodies debuts with microvascular damage and an impaired myocardial perfusion, leading to inflammation, fibrosis and, ultimately, an impaired myocardial function. This microvascular and myocardial damage may be identified early with TEM and with different diagnostic techniques commonly employed in daily clinical practice. The severity of the expected findings will progress depending on the time from the HT and will be more severe in those patients with positive anti-HLA antibodies. Specifically, we expect to find (Figure 1): Endothelial cell vacuolization, subendothelial widening and duplicated basal membranes [12].An impaired myocardial perfusion evaluated with cardiac magnetic resonance (CMR)-based quantitative perfusion sequences and with invasive parameters (a pressure guidewire) of microvascular damage (coronary flow reserve and an index of microvascular resistance) [13].Increased serum and plasmatic markers of fibrosis: fibroblast growth factor 23 (FGF-23), C-terminal propeptide of procollagen type (PICP) and collagen type 1 C-terminal telopeptide (CITP) [14,15].Increased T2 recovery times in CMR T2 mapping sequences due to intracellular edemas and increased native T1 recovery times and calculated extracellular volume as a sign of myocardial fibrosis [16].Subclinical parameters of a myocardial dysfunction (reduced global longitudinal strain in transthoracic echocardiography) [17].Signs of coronary allograft vasculopathy in patients with long-term exposure, including a reduced fractional flow reserve (guidewire pressure) and increased intimal thickness (intravascular ultrasound (IVUS)) [18].Diastolic and systolic dysfunctions in patients with an established chronic rejection.

To evaluate these hypotheses, we propose the following study objectives: Primary objective: To determine whether, in HT patients, a structural graft injury is modified or accelerated in patients exposed to anti-HLA antibodies compared with non-exposed contemporary HT patients through a thorough evaluation with TEM, OM and IHC techniques.Secondary objectives:
○An assessment of the predictive performance of different diagnostic tools (CMR, transthoracic echocardiography, serum markers of fibrosis, intracoronary pressure guidewire and IVUS) to detect tissue damage using TEM, OM and IHC techniques as the combined reference standard. ○An estimation of the risk of adverse outcomes as a function of time from anti-HLA antibody positivity.

### 3.2. Study Population

Our study base is a large dynamic cohort of HT patients assembled in the region of Madrid, Spain. All patients have received an HT and continue their follow-up in one of the three participating centers: University Hospital 12 de Octubre; University Hospital Gregorio Marañón; and University Hospital Puerta de Hierro. The local protocols for the follow-up and treatment of the HT patients are equivalent for the three participating centers. 

For every HT patient in whom anti-HLA antibodies are detected at or since the start of the study (exposed), we will select a comparator (non-exposed) with negative anti-HLA antibodies, a normal functioning graft and whose HT date is close to that of the exposed patient (Figure 2).

A confirmatory test for every patient with positive anti-HLA antibodies will be performed at least three months after the first determination and before the multimodal assessment. A regular anti-HLA antibody determination is performed as part of the local follow-up protocols for HT patients to confirm the patient allocation before evaluating the outcomes for the secondary endpoint. 

All patients will be appropriately informed about the risks of the scheduled test. For the selection of non-exposed patients, we will prioritize those patients who had a routine assessment planned within the local follow-up protocol (especially for the invasive tests).

With the inclusion of a contemporary case of an HT comparator patient (with negative anti-HLA antibodies), we will reduce the possibility of a bias induced by shorter or longer follow-up periods that may under- or over-estimate the effect of anti-HLA antibodies in myocardial injuries. The inclusion and exclusion criteria are defined in Table 1. 

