**Figure 3 mps-05-00075-f003:**
[figure not shown]
Study timeline and milestones.

**Table 1 mps-05-00075-t001:** Inclusion and exclusion criteria.

Inclusion Criteria	Exclusion Criteria
**For Exposed Patients**	Recipient of a second HT Multiple organ transplantation Unknown immunological history Recipients sensitized with anti-HLA antibodies against donor HLA before HT CMR contrast not administered with GFR < 30 mL/min/1.73 m^2^ Patients with implantable cardiac devices who did not undergo a CMR study
- Recipient of a first HT - De novo anti-HLA detection: Mean fluorescence intensity > 2000 (DSA) Standard fluorescence intensity > 150,000 (NDSA) - Detailed immunological history: Anti-HLA assessment before HT Serial assessment during HT follow-up - Known HLA typing of donor	

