**For Non-Exposed Patients**	
Recipient of a first HT Negative anti-HLA antibodies HT contemporary to the index case	

CMR: cardiac magnetic resonance; DSA: donor-specific antibodies; GFR: glomerular filtration rate; HLA: human leukocyte antigen; HT: heart transplantation; NDSA: non-donor-specific antibodies.

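### Section 3.2 requires a normally functioning graft of comparators only; Table 1 does not, and the one-sided rule tilts function-related contrasts towards antibody harm

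*Protocol article*

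**What the plan says.** Section 3.2 starts from the exposed patient: "For every HT patient in whom anti-HLA antibodies are detected at or since the start of the study (exposed"). For each one, "we will select a comparator (non-exposed) with negative anti-HLA antibodies, a normal functioning graft and whose HT date is close", where closeness is judged against the exposed patient's transplant. The comparator thus meets three conditions, one of them on graft function. The exposed patient enters on antibody detection.

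Section 3.2 then refers to Table 1 for the inclusion and exclusion criteria. Table 1 gives the non-exposed criteria as "Recipient of a first HT Negative anti-HLA antibodies HT contemporary to the index case". Graft function is not among them. It is also absent from the exposed criteria and from the exclusion list.

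The primary objective in section 3.1 asks whether "a structural graft injury is modified or accelerated in patients exposed to anti-HLA antibodies compared with non-exposed contemporary HT patients", again without a condition on function.

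The same section describes injury as starting with microvascular damage and "leading to inflammation, fibrosis and, ultimately, an impaired myocardial function". Its list of expected findings includes reduced longitudinal strain and "Diastolic and systolic dysfunctions in patients with an established chronic rejection". Section 3.5 includes strain, heart failure and death among the variables for the secondary objectives.

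**The concern.** There are two linked problems.

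First, the article leaves open who is an eligible comparator. A centre working from section 3.2 would pass over an antibody-negative patient with graft dysfunction, and a centre working from Table 1 would accept that patient. The two rules define different comparison populations, and the primary objective matches the Table 1 version.

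Second, if the section 3.2 rule is the one applied, it acts on one group only and on a variable that the study regards as a consequence of injury. Antibody-negative patients whose grafts have been injured enough to lose function are removed, while antibody-positive patients in the same state stay in. The comparison is then no longer exposed versus non-exposed contemporary recipients. It is all exposed versus the better-functioning part of the non-exposed. Some difference would be expected even if antibodies did nothing.

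**Working it through.** **The plan's own figures.** Section 3.3 plans 21 per group for 0.29 versus 0.71 (two-sided alpha 0.05, power 0.80). The arcsine formula, n = 2[(1.960 + 0.842)/h]² with h = 2·asin√0.71 − 2·asin√0.29 = 0.867, gives 21; the pooled normal formula gives 22. For the secondary rates 0.27 and 0.60 both methods give 35, as stated. The sample size is not in dispute.

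**Is the asymmetry real?**

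| Source | Comparator | Exposed |
|---|---|---|
| Section 3.2 | antibody-negative, normal graft function, close HT date | antibodies detected |
| Table 1 | first HT, antibody-negative, contemporary HT | first HT, de novo antibodies above threshold, immunological history, donor typing |
| Primary objective | non-exposed, contemporary | exposed |

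The function condition appears in one cell only.

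**Does anything in the article offset it?** Matching on transplant date deals with follow-up time. Blinded reading (section 3.4) deals with measurement. Multivariable analysis (section 3.6) cannot recover patients who were never sampled: under the rule no comparator has dysfunction at selection, so the groups do not overlap on that variable.

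**Direction and size.** Let p be the true injury prevalence, d1 the probability of dysfunction in an injured graft and d0 that in an uninjured graft. Among comparators kept because function is normal, the injury prevalence is

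q = p(1 − d1) / [p(1 − d1) + (1 − p)(1 − d0)].

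With no antibody effect, the unrestricted exposed group has prevalence p. The spurious odds ratio is therefore (1 − d0)/(1 − d1), whatever p is. It exceeds 1 whenever d1 > d0, which is what section 3.1 hypothesises.

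Inputs:
- p = 0.29, the non-exposed rate in section 3.3, taken here as the true prevalence in both groups.
- n = 40 per group, from 45 recruited less 10% dropout (45 × 0.9 = 40.5).
- d1 and d0 are assumptions. The documents give neither.

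The rejection rate is for the two-sided pooled two-proportion z-test at 5%, by normal approximation.

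| d1 / d0 | q | p − q | Odds ratio | Rejection rate |
|---|---|---|---|---|
| 0.20 / 0.05 | 0.232/(0.232 + 0.6745) = 0.256 | 0.034 | 0.95/0.80 = 1.19 | 6.3% |
| 0.40 / 0.10 | 0.174/(0.174 + 0.639) = 0.214 | 0.076 | 0.90/0.60 = 1.50 | 12.2% |
| 0.60 / 0.10 | 0.116/(0.116 + 0.639) = 0.154 | 0.136 | 0.90/0.40 = 2.25 | 30.9% |
| d1 = d0 | 0.290 | 0 | 1.00 | 5% (nominal) |

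Exact binomial enumeration gives 6.2%, 12.1% and 31.4% for the first three rows. Most of these rejections point towards antibody harm: by the normal approximation 5.3 of the 6.3 points in the mildest case, and nearly all in the other two.

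**The case against.** The strongest reply is that the study looks for early, subclinical injury. Section 3.1 says damage may be seen early with electron microscopy, and section 2 says that new antibodies with an otherwise normal work-up are relatively common. If most injured grafts still function normally, d1 is close to d0 and the bias is small. This stands as an argument about size: the mildest row is close to nominal, and the larger rows need 40% to 60% of injured grafts to be overtly dysfunctional. It does not change the direction, and it does not explain why the condition is placed on one group only.

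A second reply is that Table 1 is silent on function and does not say that dysfunctional comparators are allowed. If Table 1 governs, the bias may never arise. That is fair, and it is why the first step is to reconcile the passages.

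A third is that this is a self-described pilot with descriptive analyses, and that section 1 names the selection of non-exposed patients as a limitation. That statement does not mention graft function, and the primary objective is comparative.

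Four stronger readings are tempting and are not supported:
- **Comparators are selected on the primary outcome itself.** They are not. The primary outcome is biopsy-based structural injury, and selection is on a downstream consequence of it.
- **Every contrast is biased.** Risk as a function of time from antibody positivity does not rest mainly on comparators. The point concerns exposed versus non-exposed contrasts of outcomes related to graft function.
- **Diagnostic accuracy is inflated.** The reference standard is microscopy and immunohistochemistry, not exposure status. The rule alters the spectrum of patients, but dropping overtly injured grafts could also lower apparent sensitivity.
- **Selection could account for the planned effect.** The planned rates correspond to an odds ratio of (0.71/0.29)² = 6.0, well above the range shown here.

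**Conclusion.** The point holds in this form. Section 3.2 places a graft-function condition on comparators only, and Table 1 and the primary objective do not contain it. If it is applied, and dysfunction is more frequent in injured than in uninjured grafts as the study hypothesises, injury prevalence among comparators is understated. Contrasts of structural injury, strain and other function measures, and heart failure or death then shift towards antibody harm. For the clinical outcomes, comparators also begin follow-up already selected for good function.

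The direction follows from the article's own causal account. The size does not: the range in the table rests on dysfunction rates that the documents do not give, on a common true prevalence of 0.29 and on 40 evaluable patients per group.

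**What to change.** Delete the normal-graft condition from section 3.2 so that comparators follow Table 1: the antibody-negative recipient with the closest transplant date, whatever the graft function. Section 3.2, Table 1 and the primary objective then agree.

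If comparators have already been enrolled under section 3.2 (section 3.4 speaks of milestones achieved):
- Add a sensitivity analysis restricted to normally functioning grafts in both groups. Echocardiography, CMR and right-heart catheterization are planned for every participant, so it needs no new measurement.
- State that this restriction conditions on a consequence of injury and may understate a true effect. It complements the main analysis and does not correct it.
- Limit the main claim to a comparison with antibody-negative recipients who have normal graft function.

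Before enrolment the cost is one sentence. After enrolment it is one additional analysis and a narrower conclusion, because the sampled comparators cannot be changed. The downside of deleting the condition is that some comparators will have dysfunction from other causes, so the observed contrast may be smaller. That is nevertheless the contrast the primary objective asks about.
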